#### Individual Relationships Among the Obtained Multidimensional Data

Normally distributed data will be presented as mean (SD), median (IQR), and number (%), and nonnormally distributed data will be presented as IQR and number (%). The Kolmogorov-Smirnov test will be used to test whether the values of the variables are normally distributed. Analyses of both per-protocol and intention-to-treat groups will be conducted. The areas under the receiver operating characteristic curve (AUCs) and incremental AUCs will be calculated according to the trapezoidal rule from the measurements at each time point during the oral glucose tolerance test. Regression analysis will be used to explore the independent effects of each variable on secondary outcomes. We will examine the relationships among the overall outcomes. Correlations among the overall outcomes will be evaluated using both Pearson correlation coefficient and Spearman rank correlation. In addition, appropriate stratification and partial correlation analyses will be performed in the overall interaction analysis. All statistical analyses of the data will be performed using SPSS software (version 21.0; IBM Corp), SAS (version 9.4; SAS Institute Inc), and R software (R Foundation for Statistical Computing).

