### Microbiota Analysis

Intestinal microbiota analyses were performed as previously reported [70,71]. Briefly, the participants were instructed to use an FS-0002 tube kit (TechnoSuruga Laboratory Co Ltd) containing guanidine thiocyanate solution to collect fecal samples and store them in a refrigerator (≤4 °C) between visits. Zirconia beads were added to the samples, milled at 5 m/s for 2 minutes using a FastPrep 24 Instrument (MP Biomedicals), and centrifuged for 1 minute at 2350 × g. Bacteria were identified on the basis of the 16S recombinant DNA V3-V4 region. Fragments of the polymerase chain reaction (PCR) mixtures were purified by electrophoresis on 1% agarose gels, followed by PCR Cleanup Filter Plates (Merck Millipore). Illumina paired-end sequencing was performed using the 2 × 300 cycle paired-end method and the MiSeq system (Illumina).

Skin microbiota were collected from the scalp and cheek. To collect scalp microbiota, the hair was parted with a rubber-gloved hand to expose the frontal area of the scalp, and to collect facial skin microbiota, a custom-made sampling template was used to allow for consistent sampling of 4 cm^2^ of the cheek areas. A sterile swab (Nippon Becton Dickinson Company, Ltd) soaked in BBL-prepared saline solution (Becton, Dickinson and Company) was rubbed onto the scalp surface or the designated cheek areas. The head of the swab was cut and placed into a microtube. All samples were frozen at −80 °C until use. The V1-V2 hypervariable region was used as the target for 16S ribosomal RNA (rRNA) gene sequencing. DNA extraction, DNA library preparation, and DNA sequencing were performed by BIKEN Biomics Inc using their standard procedures.

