To analyze the saliva microbiota, part of a whole saliva pellet resuspended in sterile water was collected in a 1.5-mL tube and centrifuged for 10 minutes at 15,000 × g at 4 °C. After removing the supernatant, the pellet was stored at −80 °C until the samples were analyzed by Genome Lead Co, Inc. DNA was extracted from each sample using both enzyme treatment and the beads-beating methods (Promega). Then, DNA was extracted from the samples using zirconia beads (EZ-Beads; Promega) and Genfind v2 (Beckman Coulter). The composition of the saliva microbiota was assessed by high-throughput sequencing of the 16S rRNA gene of the V1-V2 region using the Illumina NovaSeq Platform (Illumina). The V1-V2 regions of the 16S rRNA genes from each sample were amplified using primers containing 1 random base sequence at the N position. The 2× KAPA HiFi HotStart ReadyMix (KAPA Biosystems) was used for amplicon PCR and index PCR. Both the PCR products were purified using AMPure XP beads (Beckman Coulter). The amplicon PCR products were purified using AMPure XP beads (Beckman Coulter). NovaSeq sequencing was performed using the NovaSeq 6000 Reagent Kit v1.5 (500 cycles; Illumina) using a 251-bp paired-end sequencing protocol. All 16S rRNA raw sequence data were analyzed using the open-source QIIME2 platform [72], version 2021.2 (qiime2-2021.2).

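### Pearson and Spearman correlations on 16S bacterial profiles will show closure artefacts between taxa of one site, unless another document sets a compositional scale

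*Protocol article*

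**What the plan says.** The section on individual relationships in the protocol article names the estimators for all outcomes together: "Correlations among the overall outcomes will be evaluated using both Pearson correlation coefficient and Spearman rank correlation". It adds "In addition, appropriate stratification and partial correlation analyses will be performed in the overall interaction analysis" and "Regression analysis will be used to explore the independent effects of each variable on secondary outcomes". No data type is exempted, and no transformation is named for any assay.

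The Microbiota Analysis section describes four bacterial profiles, all by 16S amplicon sequencing. For faeces, "Bacteria were identified on the basis of the 16S recombinant DNA V3-V4 region". For scalp and cheek, "The V1-V2 hypervariable region was used as the target for 16S ribosomal RNA (rRNA) gene sequencing". For saliva, "The composition of the saliva microbiota was assessed by high-throughput sequencing of the 16S rRNA gene of the V1-V2 region". On processing it says "All 16S rRNA raw sequence data were analyzed using the open-source QIIME2 platform" and gives no output scale (counts, shares, log-ratios or diversity indices). It names no measurement of absolute bacterial load at any site.

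The Objective section makes the search for relationships the secondary objective and calls it exploratory.

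**The concern.** The read total of a 16S sample is set by the sequencer, not by the bacterial load. Such a profile says how large one taxon is relative to the others and nothing about absolute amount. Expressed as shares, the taxa of a site sum to one, so a rise in a dominant taxon pushes the other shares down even if those bacteria have not changed. Pearson picks this up in the values and Spearman in the ranks, so the second coefficient does not guard against the failure of the first.

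Two kinds of result are exposed. Correlations between taxa of one site can be flagged although the taxa vary independently. And a health variable that is truly related to a dominant taxon can appear related to taxa with which it has no link.

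This is bias, so a larger sample does not reduce it. The Strengths and Limitations section expects the search to turn up new relationships that lead to hypotheses and intervention studies, so artefacts could be followed up.

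**Working it through.** The plan states no figure on this point, so there is none to reproduce. From the documents come n=997 enrolled, the two coefficients and the 16S assays. Everything about abundances is assumed, because the documents give no abundance distribution and no number of taxa.

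**Flagging threshold.** Two-sided 5%: critical |r| = 1.96/√997 = 1.96/31.58 = 0.062. Very small correlations are flagged.

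**Independent taxa turned into shares.** Simulation with n=997, 50 independent log-normal taxa, log SD 1 and one taxon made more abundant:

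| Mean share of dominant taxon | Dominant vs unrelated taxon, mean r (Pearson / Spearman) | Independent pairs flagged (Pearson / Spearman) |
|---|---|---|
| 2% (all equal) | -0.02 / -0.01 | 6% / 5% |
| 17% | -0.13 / -0.15 | 7% / 17% |
| 33% | -0.22 / -0.28 | 17% / 84% |
| 47% | -0.29 / -0.39 | 53% / 100% |

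A second set of assumptions (10, 50 or 200 taxa with unequal means, 20,000 reads per sample) gave 11-65% (Pearson) and 22-100% (Spearman) of independent pairs flagged, against 3-5% on the absolute log scale. A third (10 to 150 taxa, sampled reads with zeros) gave 29-77% and 53-98%.

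**Taxa against a health variable.**
- Variable independent of every taxon: 4-10% of taxa flagged by Spearman on shares, with no systematic excess over 5%.
- Variable correlated 0.3 with the log abundance of the dominant taxon only (50-taxon model of the table): other taxa flagged rise from 20% (Pearson) and 32% (Spearman) at a 17% share to 79% and 96% at a 47% share. After a centred log-ratio the figure is 5-6%.

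**Multiplicity.** All pairs among 1000 variables number 1000 × 999/2 = 499,500. Bonferroni at 0.05/499,500 = 1.0 × 10⁻⁷ needs |r| above about 0.168. Testing one variable against 1000 others needs about 0.128.
- Dominant taxon against other taxa: -0.22 to -0.39 (shares of 33% and 47%) passes both thresholds. At a 17% share, -0.13 and -0.15 do not pass the all-pairs one.
- Health variable linked to a dominant taxon with a 56% share: the mean correlation with an unrelated taxon is -0.10 (Pearson, p=0.0016) and -0.14 (Spearman, p=0.000009). Neither passes the all-pairs threshold, and only the Spearman value passes the one-against-1000 threshold.

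**Does a centred log-ratio cure taxon pairs?** Its k values sum to zero in each sample. For k independent taxa of equal log variance v and common covariance c, k·v + k(k-1)·c = 0, so r = c/v = -1/(k-1). The flagged share is about Φ(|r|√997 - 1.96) + Φ(-|r|√997 - 1.96):
- k=10: r=-0.111, |r|√997=3.51, Φ(1.55)+Φ(-5.47)=0.94
- k=50: r=-0.0204, |r|√997=0.644, Φ(-1.32)+Φ(-2.60)=0.10
- k=200: r=-0.0050, |r|√997=0.159, Φ(-1.80)+Φ(-2.12)=0.05

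The simulations agree: 90-94%, 10% and 5-6%. With 10 taxa the transform is worse than raw Pearson (64-65%). A SparCC-type measure, which works from variances of log-ratios, flagged 4-7% of independent pairs across 10 to 150 taxa.

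For a health variable linked to the dominant taxon, centred log-ratio values flagged 18-27% of the other taxa with 10 taxa, 6-7% with 50 and 5-7% with 200. A full panel also has a singular covariance matrix (50 taxa give rank 49), so it cannot enter a partial correlation or regression as a whole.

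**The case against.** The strongest objection is that the error is inferred. The article names the coefficients but not the scale on which taxa enter them. Pearson on log-ratio values would be compatible with its wording, and normalisation of sequencing data is commonly left to the full protocol or SAP. This stands in part. A reader might infer that the plan will correlate untransformed shares; the article does not say so, and the point is therefore conditional. What remains is that the article commits to two estimators for every outcome, and for taxon pairs a centred log-ratio before Pearson does not repair them when taxa are few. There a different estimator is needed, so this is more than a missing preprocessing note.

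Three stronger readings are tempting and not supported:
- That health variables in general will show spurious links to taxa. A variable linked to no taxon shows no inflation; a true link to a dominant taxon is required.
- That the artefacts as a class survive multiplicity control. Only correlations of a dominant taxon with other taxa are shown to do so, and only where dominance is marked. False-discovery control was not examined.
- That the distortion is large at all four sites. The documents give no abundance distribution for any site, and with even abundances it is negligible.

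It is also fair that no confirmatory claim rests on these correlations. Nothing here supports a change to the generative model, for which the VHGM Analysis section chooses a likelihood by attribute type.

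**Conclusion.** The point holds in conditional form. If no other document sets a compositional scale, the stated coefficients will give closure artefacts for taxon pairs within a site, and Spearman offers no protection. Links to other variables are distorted only where the variable is truly related to a dominant taxon.

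The size cannot be fixed from the documents. Across the assumed scenarios the share of independent pairs flagged at the 5% level runs from about 5% (50 equally abundant taxa) to nearly 100% (strong dominance, Spearman). These percentages rest on independent log-normal abundances and illustrate the mechanism; they do not predict this study's results. The analysis concerned is secondary and exploratory, so the point is modest, but it is cheap to settle.

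**What to change.** If the full protocol or SAP already sets a compositional scale for taxa against other variables and a suitable measure for taxon pairs, cite it. Otherwise:

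- **Taxon pairs within one site:** replace Pearson and Spearman with a log-ratio-variance measure, of SparCC type or proportionality.
- **Taxa against other variables:** use centred log-ratio values at a taxonomic level with many taxa (tens or more), with a stated zero replacement and a sensitivity run on that choice.
- **Partial correlation and regression:** do not enter a full centred log-ratio panel. Enter one taxon at a time, or drop a taxon or choose a reference.
- **Generative model:** make no change to the HIVAE inputs on this ground.

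The cost is a short addition to the analysis plan, a zero-handling choice to defend and a small amount of extra code. No new data are needed.

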## Results

The study was registered at University Hospital Medical Information Network on October 14, 2021. Recruitment was started on October 19, 2021, and ended on February 25, 2022. A total of 997 participants were enrolled in the study. Sample analysis will be performed from February 2022 to March 2023. Data analysis will be conducted in 2023, and the final report will be available in 2024.

## Discussion

### Principal Findings

High-dimensional cross-sectional studies are rarely conducted. We believe that there are several methods to use such data sets. We plan to provide the VHGM that we are developing as a commercial service via an application program interface (API) on the internet. Any application program can send a query to the VHGM, such as *what is the mean and variance of systolic blood pressure of Japanese adults? (marginal probability)*; *what is the probable distribution of blood glucose levels given my age, sex, and lifestyle (excursive, drinking, and smoking habits)? (conditional probability)*; and *what would my estimated cognitive function index be if my age were 10 years older (counterfactual inference)*. We are expecting to discover many innovative health care applications using the VHGM API.

### Strengths and Limitations

Our exploration of individual relationships among the thousands of variables in the data set is expected to reveal previously unknown relationships, which may lead to a new health care hypotheses and further studies, including those aimed at constructing new intervention tests. Thus, this cross-sectional data set will lead to new discoveries in health care research.

Limitations of this protocol include its cross-sectional study design at a point in time, the fact that recruitment (via a website) was restricted to those who could participate in person to perform the survey. In addition, our sampling methods, such as the study’s inclusion criteria and the decision by the responsible physician whether to allow participation, may have introduced a selection bias, making it difficult to generalize our findings to the population. Appropriate weighting can be applied to reduce the impact of selection bias on the estimates. If any modifications to this study design are necessary, we will notify the IRB and submit a study protocol with the necessary changes for IRB review. Thus far, data on preventive medicine and health care have been obtained on an opportunistic and time-consuming basis, using funds as needed. The data obtained from this study have the potential to provide a standardized model for the Japanese population regarding health care and to reveal public health implications. Using a larger sample size would reduce the risk of type II errors.

### Conclusions

The results of this study may provide evidence for the future application of a VHGM based on a joint probability distribution model in clinical health care practice.

## Abbreviations

AGE: advanced glycation end product
APDS: 3-aminopyridyl-N-hydroxysuccinimidyl carbamate
API: application program interface
AUC: area under the receiver operating characteristic curve
FU: follicular unit
HIVAE: heterogeneous incomplete variational autoencoder
HPLC: high-performance liquid chromatography
IL: interleukin
IRB: institutional review board
LC: liquid chromatography
LC-MS/MS: liquid chromatography–tandem mass spectrometry
LC-MS: liquid chromatography–mass spectrometry
MS: mass spectrometry
PCR: polymerase chain reaction
rRNA: ribosomal RNA
SPME-GC-MS: solid-phase microextraction–gas chromatography–mass spectrometry
SSL: skin surface lipid
STROBE: Strengthening the Reporting of Observational Studies in Epidemiology
UMIN: University Hospital Medical Information Network
VHGM: Virtual Human Generative Model
